**Variant 3. If the risk is increased two to three times (moderate increase in risk compared to the same age average):**

- Implement mammography screening at **two-year intervals** from the age at which the risk of the average 50-year-old woman is reached (depending on the age at which the 10-year risk reaches 2.1 %).

and/or

- Implement mammography screening at one-year intervals from the age at which the average 50-year-old woman reaches twice the risk level (depending on the age at which the 10-year risk exceeds twice the corresponding age level or for women under 50 from the risk level of  $2 \times 2.1$  %, which is twice the risk level for women aged 50);

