## **STEP 4. Implementation of personalized screening and prevention (risk reduction)**

### **Next steps after test results**

#### **Personalized Prevention Measures Based on the AnteBC test**

Based on the PRS, it is possible to divide the patient's relative risk of developing BC into different levels compared to the average in the given age, while accurately assessing the risk of a particular percentile. The women will be recommended annual or biennial mammography examination according to risk level and Variant 1-4 listed in Step 3.

The population-based screening program has a central organization with a standardized regime for an invitation, screen-reading, and registration of screening results. Modification of screening logistics as entry age or screening frequency is not possible within the screening program as such. Thus, for women recommended mammographic screening starting at an earlier age (<50) and/or increased frequency (annual screening), these “extra” examinations will be offered as a clinical mammography examination outside the screening program.

The women will be followed for 10 years.

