### **Cost-effectiveness analyses**

During the final stage (last 6 months) of the pilot study, the cost-effectiveness analysis will be conducted.

The cost-effectiveness analysis will aim to estimate the difference in health outcomes and the difference in costs of implementing the personalized medicine interventions as compared to standard care.

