#### Methodology of the cost-effectiveness study

Whereas the whole pilot study aims to develop models for the personalized medicine interventions, it is not possible to predict which efficacy and effectiveness measures will be best suited to estimate the health outcomes of the program.

The planned personalized medicine interventions are preventive, and the pilot project will last less than 2.5 years, thus the most robust health outcome of mortality cannot be achieved during the study. Therefore, additional health outcomes, e.g. disease-free time to diagnosis and/or hospital care, stage of cancer diagnosed will be used to estimate the effect of preventive measures to increase the disease-free life years, postpone the negative health events, and decrease the need to use health care resources will be collected. This data will be used to model the number of events occurring in specified cohorts of persons at risk – a cohort receiving personalized preventive interventions will be compared to that on standard care.

To estimate the long-term effectiveness and costs of the new interventions, economic modeling will be used. The Markov cohort models of the natural history of BC will be constructed to assess the cost-effectiveness of preventive interventions.

The recently published cost-effectiveness studies modelling BC will be used to construct the natural history of the disease. Annual age-specific probabilities of dying from this disease and the health-related quality of life decrement during the illness will be calculated for the Swedish, Estonian and Portuguese cohorts using published cost-effectiveness studies.

The analysis results will be presented as incremental costs and quality-adjusted life-years (QALYs) gained with each intervention compared to no personalized medicine and as incremental cost-effectiveness ratios (ICERs). Both costs and utilities will be discounted at an annual rate of 5%. The sensitivity analysis will be performed by varying one or more similar parameter(s) at a time while holding other parameters at their base case value.

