#### The data used for cost calculations will include

- Direct costs of the use of health care services (out-patient care, hospital care, and pharmaceuticals), based on the data from healthcare systems.
- Costs for developing and maintaining IT solutions for collecting and using health information for personalized medicine purposes.
- Costs for collection and analysis of additional samples arising from the new clinical approaches of the two preventive interventions.
- Costs for disseminating the results of the pilot project to the scale of the whole population: training of health care staff and additional workload estimates related to full implementation of the personalized medicine approach (e.g. motivational interviewing).

Most of this cost data will be collected in parallel to the implementation of the pilot project.

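### The cost-effectiveness results are planned for each of several undefined interventions with one common baseline as the only comparator; if mutually exclusive strategies are modelled, an inefficient added step could be hidden

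*Protocol*

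**What the plan says.** Under *Cost-effectiveness analyses* (protocol, Section 6.2), one part of the aim is to estimate "the difference in costs of implementing the personalized medicine interventions as compared to standard care". The interventions are in the plural and there is one comparator.

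The *Methodology of the cost-effectiveness study* then describes two modelled groups: "a cohort receiving personalized preventive interventions will be compared to that on standard care". The same section sets the form of the results: incremental costs and QALYs "gained with each intervention compared to no personalized medicine and as incremental cost-effectiveness ratios". No other comparator is named for the ICERs. The planned sensitivity analysis varies model parameters around their base-case values and does not compare one strategy with another.

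The list of cost data refers to "the new clinical approaches of the two preventive interventions". That bullet concerns the cost of collecting and analysing additional samples, and the two interventions are not defined there or elsewhere.

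The programme itself has graded intensity. Step 4 of Section 5.2 states: "The women will be recommended annual or biennial mammography examination according to risk level and Variant 1-4 listed in Step 3". In Variants 3 and 4 of Step 3, a two-year schedule that starts when the 10-year risk reaches 2.1% is joined by and/or to a second item: "Implement mammography screening at one-year intervals from the age at which the average 50-year-old woman reaches twice the risk level".

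**The concern.** When several strategies compete for the same women, so that only one can be adopted, the ratio of each to a shared baseline is an average over all the steps up to that strategy. It does not show what the last step buys. A more intensive strategy can have an acceptable ratio to the baseline because a cheaper, efficient first step supplies most of the gain. The usual remedy is to order the strategies by cost, remove those that are dominated, and compare each remaining one with its neighbour.

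Section 3.7 states as a key hypothesis that the programme is cost-effective. If several competing strategies were modelled and only ratios to the common baseline were presented, that hypothesis could be judged on a figure that does not show whether the most intensive part is worth its cost. The planned sensitivity analysis would not reveal this, because it changes inputs and not the comparison.

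**Working it through.** **No figure to reproduce.** The protocol gives no cost, QALY gain, ICER or willingness-to-pay threshold. Only the mechanism can be checked, on assumed inputs.

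**Step 1: the algebra.** Let the less intensive strategy against the baseline have increments (dC1, dE1), and the added step increments (dC2, dE2).

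- Less intensive strategy against baseline: dC1/dE1.
- More intensive strategy against baseline: (dC1 + dC2)/(dE1 + dE2), the QALY-weighted average of dC1/dE1 and dC2/dE2.
- Added step alone: dC2/dE2.

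Write m = dC2/dC1 and f = dE2/dE1. The added step's ICER divided by the common-baseline ICER is m(1 + f) / [f(1 + m)]. It exceeds 1 only when m > f, that is, when the added step yields fewer QALYs per unit cost than the first.

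**Step 2: one worked case (assumed inputs).** Take dC1 = 1,000 cost units and dE1 = 0.05 QALY, so the first step costs 1,000/0.05 = 20,000 per QALY. Let the added step cost as much again (m = 1) and add 20% of the first gain (f = 0.2, so dE2 = 0.01).

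- More intensive against baseline: 2,000/0.06 = 33,333 per QALY.
- Added step alone: 1,000/0.01 = 100,000 per QALY.
- Ratio: 3.0.

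**Step 3: the range.** Ratio of the added step's ICER to the common-baseline ICER:

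| m | f = 0.1 | f = 0.2 | f = 0.25 | f = 0.5 | f = 1 |
|---|---|---|---|---|---|
| 0.5 | 3.67 | 2.00 | 1.67 | 1.00 | 0.67 |
| 1 | 5.50 | 3.00 | 2.50 | 1.50 | 1.00 |
| 2 | 7.33 | 4.00 | 3.33 | 2.00 | 1.33 |

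How many cells lie above 1 reflects the grid chosen, not how likely each case is.

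**Step 4: the reversed case.** At m = 0.5 and f = 1 the first step costs 20,000 per QALY, the added step 500/0.05 = 10,000, and the two together 1,500/0.10 = 15,000. The less intensive strategy is then extendedly dominated and drops out. The more intensive one is properly compared with the baseline, at 15,000. Here the common-baseline figure for the more intensive strategy is the right one.

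**Step 5: the role of the test cost.** The cost of risk testing falls on the first step. Suppose the examinations cost 1 unit on the more intensive schedule and 0.5 on the less intensive one, testing costs T, and the less intensive schedule gives a share g of the full gain. The added step's ICER is 0.5/(1 − g), the common-baseline ICER is T + 1, and the ratio is 0.5/[(1 − g)(T + 1)]. It falls below 1 when T > 0.5/(1 − g) − 1:

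- g = 0.7: T above 0.67.
- g = 0.6: T above 0.25.
- g = 0.5: any positive T.

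The protocol gives neither T nor g, so the direction stays open.

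**Step 6: does the protocol contain competing strategies?** The passages point both ways. The plural wording under *Cost-effectiveness analyses*, the reporting rule and the cost list suggest more than one intervention. The cohort description suggests a single programme against standard care. The intervals are assigned by risk level, so tiers given to different women are not alternatives to each other. Within Variants 3 and 4, both intervals are linked to the same risk group. A programme with the one-year step and one without it would be mutually exclusive policies.

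**The case against.** The strongest reply is that the protocol nowhere makes annual and biennial mammography the interventions whose ICERs are reported. A reader might infer this from the graded schedule and from the mention of two preventive interventions, but the documents do not support it. The schedule is one risk-dependent algorithm, and the mention of two interventions stands in a bullet about samples, which mammography intervals do not generate. If one programme is compared with standard care, there is no intermediate strategy and the planned ICER is already fully incremental. That part of the reply stands.

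Three further points carry weight.

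- **Recovery by subtraction.** If costs and QALYs are reported for every strategy, pairwise ICERs and dominance can be worked out from them. This is true, so the information would not be lost. It would be left to the reader, and only if the strategies were modelled separately.
- **Grammar.** The stated comparator attaches to costs and QALYs. For the ICERs it is implied.
- **Level of detail.** Naming modelled strategies can be left to an analysis plan, and this is one of many secondary outcomes in an 80-woman pilot. That limits the weight of the point. It does not remove it, because the protocol does state a reporting rule with a named comparator, in wording that conflicts with its own cohort description.

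A reader might also infer that the planned ratio necessarily flatters the most intensive screening. Steps 4 and 5 of the working show that it need not.

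**Conclusion.** The point holds in conditional form. The protocol fixes a presentation by intervention, names a single common baseline, and leaves the interventions undefined, with plural wording beside a one-programme cohort description. If mutually exclusive strategies are modelled, that presentation averages the steps and can hide an inefficient added one. If one programme is modelled, the planned ICER is appropriate and only the wording needs to be made consistent.

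No size can be assigned from the document. The range of 0.67 to 7.3 rests wholly on assumed cost multiples (0.5 to 2) and QALY multiples (0.1 to 1), and it includes reversal. The primary outcome and the data collected from participants are unaffected. What is at stake is the interpretation of the cost-effectiveness hypothesis. Nothing here says which screening interval is preferable.

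**What to change.** In *Methodology of the cost-effectiveness study* (Section 6.2):

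1. Name the strategies to be modelled, and bring the references to each intervention, to two interventions and to a single personalised cohort into agreement.
2. Keep the comparison of every strategy with standard care.
3. Where two or more strategies are mutually exclusive, order them by cost and drop dominated and extendedly dominated ones. Report each remaining ICER against the next less costly remaining strategy as well. If only one programme is modelled, say so; this item then does not apply.

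The cost is a short change of text and, if several strategies are modelled, a few more runs of the same Markov model. No further participant data are needed. The drawback for the sponsor is that the most intensive step may look less favourable.

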#### The data used for cost calculations will include

- Direct costs of the use of health care services (out-patient care, hospital care, and pharmaceuticals), based on the data from healthcare systems.
- Costs for developing and maintaining IT solutions for collecting and using health information for personalized medicine purposes.
- Costs for collection and analysis of additional samples arising from the new clinical approaches of the two preventive interventions.
- Costs for disseminating the results of the pilot project to the scale of the whole population: training of health care staff and additional workload estimates related to full implementation of the personalized medicine approach (e.g. motivational interviewing).

Most of this cost data will be collected in parallel to the implementation of the pilot project.

### **6.3. Access to Data**

Direct access will be granted to authorized representatives from the Sponsor and host institution for monitoring and/or auditing of the study to ensure compliance with regulations.

## **7. QUALITY ASSURANCE PROCEDURES**

We plan data quality monitoring inside the study group, no data monitoring is planned from the third parties.

## **8. ETHICAL AND REGULATORY CONSIDERATIONS**

### **8.1. Declaration of Helsinki**

The Investigator will ensure that this study is conducted following the principles of the Declaration of Helsinki.

### **8.2. Guidelines for Good Clinical Practice**

The Investigator will ensure that this study is conducted following relevant regulations and with Good Clinical Practice.

### **8.3. Approvals**

The protocol, informed consent form, participant information sheet and any proposed advertising material will be submitted to an appropriate Research Ethics Committee (REC for written approval.

The Investigator will submit and, where necessary, obtain approval from the above parties for all substantial amendments to the original approved documents.

### **8.4. Reporting**

The CI shall submit once a year throughout the study or on request, an Annual Progress report to the REC Committee and Sponsor. In addition, an End of Study notification and the final report will be submitted to the same parties.

### **8.5. Participant Confidentiality**

The study staff will ensure that the participants' anonymity is maintained. The participants will be identified only by a participant ID number on all study documents and any electronic database, except the eCRF, where participant initials may be added. All documents will be stored securely and only accessible by study staff and authorized personnel. The study will comply with the Data Protection Act, which requires data to be anonymized as soon as it is practical to do so.

### **8.6. Expenses and Benefits**

There are no planned payments for participants.

## **9. FINANCE AND INSURANCE**

### 9.1. Funding

The project is funded by the Norway Grants “Green ICT” program and sponsored by the AnteNOR Consortium.

### 9.2. Insurance

No insurance is planned in the current project.

## 10. PUBLICATION POLICY

The Investigators will be involved in reviewing drafts of the manuscripts, abstracts, press releases, and any other publications arising from the study. Authorship will be determined following the ICMJE guidelines and other contributors will be acknowledged.

## 11. APPENDIX A: AMENDMENT HISTORY

| Amendment No. | Protocol Version No. | Date issued | Author(s) of changes | Details of Changes made |
|---------------|----------------------|-------------|----------------------|-------------------------|
|               |                      |             |                      |                         |

